#### Endpoints

Measurements of CTCs, ctDNA, cfnucleosomes, circulating proteins, EVs, CIC, and circulating microbiota as defined above.Area Under the Curve (AUC) of the ROC curve of the multi-marker *LB* signature. Optimal threshold of the multi-marker *LB* signature that maximizes the Youden index.Dichotomized test at the optimal threshold: positive test (patients with resectable PDAC) if the *LB* signature is greater than or equal to the optimal threshold/negative test (HC) if the *LB* signature is lower than the optimal threshold.*Sensitivity*: the percentage of patients with resectable PDAC (gold standard = cytologically and/or histologically proven PDAC) with a positive LB signature test.*Specificity*: the percentage of HC with a negative LB signature test.

#### Data management

The database is managed by the Montpellier Cancer Institute Data Center using the Clinsight® software. A data-management plan and a consistency check program were established during the database’s creation. Each investigator has unique usernames and passwords to access the database. A specific and secure login was established to database monitoring. Quality control of the data is conducted in four ways: *i)* automatic data consistency checks; *ii)* data management control through regular queries submissions; *iii)* regular e-control of entered data by the project manager; *iv)* on-site data monitoring of at least 10% of the entered data. A fill rate analysis plan is also regularly sent to the BACAP 2 coordinator by the data manager.

#### Highlights of the PANLIPSY project

*Patient recruitment*: *(i)* PANLIPSY relies on the well-established and nationally organized BACAP 2 network; *(ii)* Patients presenting all stages of PDAC and benign pancreatic conditions (PACTOL clinical trial) are included to define the blood signature that can detect PDAC at a very early stage;*Controls:* Healthy donors will be recruited at the end of each phases DISCOVERY & VALIDATION PHASES to be exactly age- and sex-matched;*Blood samples*: A significant volume of blood (50 mL) will be prospectively taken in dedicated tubes to analyze seven circulating biomarkers simultaneously in the same patient;*Data quality*: Clinical, radiological and biological data defined by the BACAP cohort will be considered in our signature on top of the *liquid biopsy*;*Artificial Intelligence*: At the end of the first DISCOVERY PHASE, AI-based machine learning will combine several pieces of information to identify the blood signature, which can discriminate patients developing pancreatic cancer from healthy donors and those with a benign pancreatic disease. In the VALIDATION PHASES, the *liquid biopsy* will be blindly analyzed with the newly discovered signature to validate it.*Feasibility:* The various PANLIPSY partners have already worked together successfully, even publishing a few articles [18–20]. All the technologies needed to achieve our objectives are optimized, robust and implemented daily in the various laboratories.

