#### Healthy controls

After the completion of patients’ inclusion in each phase, the INOVIE Biobank (INOSPECIMENS) will graciously provide blood samples from age- and sex-matched HCs (*n* = 85 at the end of the discovery phase then *n* = 30 for the validation phase).

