### Data collection and follow-up

Data are collected at the patient’s inclusion, during the diagnosis process, and before any cancer treatment administration (upfront surgery, chemotherapy-radiochemotherapy, and/or surgery and/or best supportive care), and through follow-up until death. As previously defined by the BACAP protocol, clinical data collected will include: disease presentation, demographic data, baseline biology, radiology, endoscopic ultrasound, tumor staging, pathology reports, treatments, follow-up (including biological and radiological), and survival [11]. Patient follow up will be managed according to standard-of-care and will depend on the practices of each center. All these data will be collected and stored through an e-observation system at a centralized data center.

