### Statistical analysis

In this project, the first type of machine learning model we will train is random forests. These will be used to predict whether a patient will develop pancreatic cancer based on all measured markers and associated health data. The dataset collected in this project will be divided into three different subsets: a training set (60% of the samples), a test set (20% of the samples), and a validation set (20% of the samples). A stratified sampling approach will be used to ensure that each class is accurately represented in each set, especially if an imbalance between classes is present in the original dataset. The training and test subsets will be used to train the machine learning algorithms, while the validation subset will be used to ensure that the model is generalizable (i.e., it can accurately classify future samples that may be collected). We will use the out-of-bag error method (a bootstrapping procedure that trains the models on multiple subsets of the predictor variables) to quantify the relative contribution of each variable to the model's performance. In addition, the performance of each model will be quantified by calculating its accuracy, precision, and area under the curve (AUC). In the performance of the random forest models is not satisfactory, the same approach will be used, but this time using XGboost and artificial neural network models instead. This approach allows the complexity of the model to be gradually increased, with the aim of forming a parsimonious model with a good ability to distinguish between healthy and cancer patients. The performance of all models trained during this project will be compared to a multiple logistic regression model as a baseline model.

We will also explore the results of machine learning models in the inferential framework. Using generalized linear models, we will compare the mean of each marker retained by the best machine learning models, while controlling for confounding variables (e.g., age…). This approach will quantify the differences in markers between healthy and cancer patients and identify markers that may not be statistically significantly different between the two groups but still contribute to good machine learning performance (those variables are called "weak predictors").

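### The article lets diagnostic work-up data enter the signature in two sections but defines the signature and its AUC as liquid-biopsy only in three others; if work-up data are used, the AUC can be high without any blood signal

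*Protocol article*

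**What the plan says.** Two sections of the protocol article bring non-blood data into the model.

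- Highlights of the PANLIPSY project, under data quality: "Clinical, radiological and biological data defined by the BACAP cohort will be considered in our signature on top of the" liquid biopsy.
- Statistical analysis: random forests will be trained to "predict whether a patient will develop pancreatic cancer based on all measured markers and associated health data".

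Three sections describe something narrower. Aims of PANLIPSY defines the signature as the combined results of the liquid-biopsy analytes. Design says the algorithm is to find the best combination of blood markers. Endpoints attaches the AUC, the Youden threshold, sensitivity and specificity to the multi-marker liquid-biopsy signature.

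Three further statements show where the data come from.

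- Data collection and follow-up lists the BACAP clinical data as "disease presentation, demographic data, baseline biology, radiology, endoscopic ultrasound, tumor staging, pathology reports, treatments, follow-up" and survival. The data are collected at inclusion, "during the diagnosis process, and before any cancer treatment administration", and then through follow-up.
- The PDAC inclusion criteria admit only cytologically or histologically confirmed cases, and Endpoints names the reference standard as "gold standard = cytologically and/or histologically proven PDAC".
- Healthy controls says the biobank "will graciously provide blood samples from age- and sex-matched HCs". No imaging or clinical work-up is described for them.

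**The concern.** The study asks whether a blood signature can detect resectable PDAC. A radiological finding from the work-up is part of how a case came to be diagnosed, and a pathology report contains the reference standard itself. If such a variable sits among the predictors, a flexible classifier can tell cases from controls by the work-up and leave the blood markers unused. If the variable is missing for controls, the missingness can do the same.

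The AUC, threshold, sensitivity and specificity would then describe the diagnostic pathway and not the liquid biopsy. As the article stands, a reader cannot tell which model those figures will belong to.

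The stated safeguards do not close the gap. Age and sex matching does not touch imaging. The 60/20/20 split and the out-of-bag error cannot detect a difference that is present in every subset. The adjusted generalized linear models are fitted after the markers have been selected and do not change the classifier. The benign group comes from PACTOL and is not part of the validation contrast.

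**Working it through.** **1. The plan's own figure.** Inputs from Sample size justification: A = 0.85, 85 resectable cases, 85 controls, two-sided 95% confidence. By the Hanley-McNeil formula:

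- A/(2 − A) = 0.85/1.15 = 0.7391
- 2A²/(1 + A) = 1.445/1.85 = 0.7811
- Variance = [0.85 × 0.15 + 84 × (0.7391 − 0.7225) + 84 × (0.7811 − 0.7225)] / (85 × 85) ≈ 6.445/7225 = 0.000892
- SE = 0.0299; 1.96 × SE = 0.0585; width = 0.117

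The article states 0.118, which is twice the rounded half-width of 0.059. The figure reproduces and is not in dispute. It sets the scale: an AUC of 0.85 is planned with an upper limit of about 0.85 + 0.059 = 0.909.

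**2. One work-up variable, no blood signal.** For a single binary predictor, AUC = (sensitivity + specificity)/2. The documents give no such sensitivities or specificities, so these are assumptions over a range:

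- 70% and 95%: (0.70 + 0.95)/2 = 0.825
- 90% and 95%: (0.90 + 0.95)/2 = 0.925
- 90% and 99%: (0.90 + 0.99)/2 = 0.945
- 100% and 100%: 1.00

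The second value already lies above both the planning AUC of 0.85 and its planned upper limit of 0.909.

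**3. A variable recorded only in cases.** If it is recorded in a share p of cases and in no control, and the coding lets the model use its absence, specificity is 1 and AUC = (p + 1)/2. At p = 0.50 this is 0.75, at p = 0.70 it is 0.85, at p = 0.90 it is 0.95, and at p = 1 it is 1.00. A panel with no signal would match the planning AUC once 70% of cases have the entry.

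**4. A blood panel with some signal.** Here a normally distributed blood score is combined with the binary variable through the optimal likelihood-ratio score. The two are assumed independent within each group. The separation of the blood score is √2 × Φ⁻¹(blood AUC), with 200,000 simulated subjects per group. Columns give the assumed sensitivity/specificity of the work-up variable.

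| Blood-only AUC | 70%/95% | 90%/95% | 90%/99% | 100%/100% |
|---|---|---|---|---|
| 0.50 | 0.82 | 0.925 | 0.945 | 1.00 |
| 0.70 | 0.89 | 0.95 | 0.97 | 1.00 |
| 0.85 | 0.94 | 0.97 | 0.98 | 1.00 |

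Read down any column: panels from useless to as good as planned become hard to tell apart. At 90%/95% the combined AUC runs only from 0.925 to 0.97 while the blood AUC runs from 0.50 to 0.85.

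**5. Validation.** The validation phase blindly classifies 30 resectable cases and 30 healthy controls, again from BACAP and the biobank. Blinding hides the label from the analyst. It does not remove an input that itself identifies the group. If the signature carries such inputs, the artefact recurs and looks like confirmation.

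**The case against.** The strongest reply is that the endpoint is blood-only. Aims, Design and Endpoints all say so, as does the abstract. The sentence in Highlights is a list item, and to say that data will be considered is not to specify a model. The next item in that list speaks of a blood signature and says that the liquid biopsy is what will be analysed blindly in validation. This stands as far as it shows that the intention may well be a blood-only endpoint. It does not remove the conflict: Highlights names radiological data as part of the signature, Statistical analysis feeds health data to the models, and nothing in the article excludes them or asks for a separate blood-only AUC.

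A reader might also infer more than the text supports:

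- That staging, endoscopic ultrasound, pathology and treatment will be predictors. The list in Data collection and follow-up describes what is recorded. It is not a predictor list, and it also holds harmless items such as demographic data. Stage has another stated use, in signatures by stage and aggressiveness. The exact list may be in a full protocol or analysis plan that is not shown.
- That these fields will be empty for controls. The article is silent on what health data accompany the biobank samples.
- That the AUC will be 1.0. This needs a case-only variable to enter the model, with its absence coded so that the model can use it. Neither is stated.
- That the study claims to forecast future cancer. The wording in Statistical analysis suggests it, but the same section states the aim as telling healthy people from cancer patients, and all cases are confirmed at inclusion. It is a slip of wording and does not bear on the leakage.

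**Conclusion.** The point holds as a contradiction with a specific bias attached. Two sections state that non-blood data enter the model or signature, and three define the signature and its performance measures without them. If work-up variables are used, the AUC, sensitivity and specificity are biased upwards as measures of the blood panel.

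Under an assumed 90% sensitivity and 95% specificity for one variable, a panel with no signal reaches 0.925. Over the assumed range it reaches 0.825 to 1.00, against a planning AUC of 0.85. The direction is secure. The size depends on which variables enter, how accurate they are, and whether controls have them, none of which the article gives. The documents do not support a flat statement that label leakage will occur or that the AUC will be 1.0. They do support the statement that nothing in the article prevents it, and that the matter should be settled before the discovery model is fitted.

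**What to change.** Reconcile Statistical analysis and Highlights with Aims, Design and Endpoints:

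- **Primary signature.** State that its candidate predictors are the blood analytes measured in the same way in PDAC, benign and healthy groups, plus age and sex if wanted. State that the endpoint AUC, threshold, sensitivity and specificity belong to this model.
- **Exclusions.** State that radiology and any other variable from the diagnostic work-up (endoscopic ultrasound, staging, pathology, treatment) do not enter the case-versus-control classifier. Stage can still be used to define groups for the stage-specific signatures.
- **Other clinical variables.** Allow them only in a secondary model, reported separately, and only if they are captured in the same way in all groups.
- **Wording.** Say that the model predicts whether a person has pancreatic cancer. This is a correction of language only.

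The cost is a change of text. Recruitment, tubes and assays stay as they are. Discovery controls are supplied after patient inclusion in that phase is complete and the model is built at its end, so a change made before then loses nothing. The one downside is that the reported AUC may be lower than with work-up data included.

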### Validation phase

Secondly, the defined combination of candidate biomarkers will be validated in the final year by blindly classifying ‘patients with early-stage/resectable PDAC (*n* = 30)’ from ‘HCs’ (*n* = 30).

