### CTC detection and characterization

Among the various CTC technologies, the CellSearch® system (MENARINI) has gained considerable attention over the past years. It is the first CTC assay cleared by the US FDA and currently the gold standard for CTC detection, and the most widely used technology for prognostic purposes in clinical studies. It is based on the enumeration of epithelial cells that are separated from whole blood samples by positive enrichment using anti-EpCAM antibodies coated with magnetic beads. Specifically, the ferrofluid reagent consists of particles with a magnetic core surrounded by a polymeric layer coated with anti-EpCAM antibodies for directly capturing CTCs. After immunomagnetic capture and enrichment, fluorescent antibodies (against cytokeratin, panCK (CK8/18/19) that are expressed in the CTC cytoplasm; and against CD45 expressed at the leukocyte surface) and the nuclear dye DAPI are added for CTC identification and enumeration. CTCs are defined as EpCAM^+^/panCK^+^/DAPI^+^/CD45^−^ cells. The 4th channel allows assessing an additional marker to characterize directly CTCs at the single-cell level.

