### Circulating immune cells

CIC analyses will be performed using enriched peripheral blood mononuclear cells (PBMCs) stained for multi-parametric FACS analyses. PBMCs will be analyzed to define and characterize various immune cell populations and to determine the expression profiles of T-cells, cytotoxic T-cells, T-regulatory cells (T-regs), natural killer (NK) cells, B-cells and immune checkpoint inhibitor. A second tube will be used to determine the monocytes/macrophages expression profile. The Zombie red™ Fixable Viability kit will be used to exclude dead cells. Samples will be analyzed by Beckman Coulter Gallios Flow Cytometry, and data will be collected with the Kaluza acquisition software and analyzed with the Kaluza software.

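### Because controls always arrive last and from another source, the stated blind secures the classification step but not the reading of assays run on receipt

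*Protocol article*

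**What the plan says.** **Blinding.** It is mentioned twice, both times for validation. The Validation phase section says the marker combination will be "validated in the final year by blindly classifying" 30 patients with resectable PDAC and 30 healthy controls. The Highlights section says: "In the VALIDATION PHASES, the *liquid biopsy* will be blindly analyzed with the newly discovered signature to validate it".

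**Supply of controls.** The Healthy controls section states: "After the completion of patients’ inclusion in each phase, the INOVIE Biobank (INOSPECIMENS) will graciously provide blood samples from age- and sex-matched HCs". The Highlights section repeats this and gives the reason: "Healthy donors will be recruited at the end of each phases DISCOVERY & VALIDATION PHASES to be exactly age- and sex-matched". The Discovery phase and Discussion sections agree.

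**Who handles the blood.** The Liquid biopsy assays section centralises blood management at one laboratory. Table 1 in the Design section assigns the CTC, EV and circulating immune cell (CIC) work to that same laboratory.

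**The assays.** On CTCs: "CTCs are defined as EpCAM^+^/panCK^+^/DAPI^+^/CD45^−^ cells". On immune cells: "PBMCs will be analyzed to define and characterize various immune cell populations". The assay sections do not say when each assay is run relative to receipt, or what the reader knows.

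**Storage.** ctDNA plasma and buffy coat are frozen at -80 °C. The Biobanking section lists stored plasma, platelets, CTCs and PBMCs, and does not mention stored whole blood.

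**The concern.** A coded label hides status only if nothing else reveals it. Here arrival time and source reveal it. In validation, every sample received before inclusion closes is a cancer case, and the controls follow as one block from another supplier. In discovery, every sample before closure comes from a patient (PDAC or benign disease), and the healthy controls follow. PDAC-versus-control status is thus inferable for anything read on arrival, by staff of the laboratory that also takes in the blood.

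If a read involves judgement, that knowledge can shift the marker values. The AUC, sensitivity and specificity in the Endpoints section are all computed from those values. Masking whoever applies the signature cannot remove a shift already in its inputs. The validation phase repeats the same order, so an offset learned in discovery would be confirmed in validation and not exposed.

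**Working it through.** **1. Can status be inferred from the order?**
- Discovery: 85 + 50 + 50 PDAC and 25 benign patients are included over 3.5 years; 85 controls follow. Total 85 + 50 + 50 + 25 + 85 = 295, as stated.
- Validation: 30 PDAC patients over a 12-month inclusion period; 30 controls follow. Total 60, as stated.
- In validation, receipt before or after closure separates the two groups completely. In discovery it separates PDAC from healthy controls, but not PDAC from benign disease.

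**2. Which assays are exposed?**
- CTCs are enriched from whole blood, and no stored whole blood is described. On this text, patient CTC samples are most plausibly processed before any control of that phase exists.
- CIC and EV reads are exposed if done on receipt. The article does not say, and stored cells and plasma would allow later runs.
- ddPCR, the automated nucleosome immunoassay, the qPCR-read protein panel, 16S qPCR and ELISA are read by instrument and are less exposed to reader judgement.

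**3. The plan's own AUC figure.** The sample size section gives a 95% CI width of 0.118 (half-width 0.059) for AUC A = 0.85 with 85 + 85. The Hanley-McNeil variance is

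[A(1−A) + (n₁−1)(Q₁−A²) + (n₂−1)(Q₂−A²)] / (n₁n₂), with Q₁ = A/(2−A) = 0.7391 and Q₂ = 2A²/(1+A) = 0.7811.

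- n = 85 per group: (0.1275 + 84 × 0.01663 + 84 × 0.05858)/7225 gives SE 0.0299, half-width 0.0585 and width 0.117. The plan's figure is reproduced.
- n = 30 per group: SE 0.0506, half-width 0.099, or about 0.75 to 0.95.

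These intervals describe sampling error. Neither covers a systematic offset between the groups.

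**4. How large could a reader offset be?** The documents give no figure, so this step is illustration under assumption. For normal, equal-variance values shifted by d SD in line with status, AUC = Φ(d/√2) when there is no true difference.

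| Assumed shift d | d/√2 | Apparent AUC, true 0.50 |
|---|---|---|
| 0.2 | 0.141 | 0.556 |
| 0.3 | 0.212 | 0.584 |
| 0.5 | 0.354 | 0.638 |

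If the shift acts on a score with true AUC 0.75 (Φ⁻¹ = 0.6745), the apparent AUC is Φ(0.6745 + d/√2) = 0.793, 0.812 and 0.848. At 0.5 SD it would look like the planning value of 0.85.

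For k equally shifted markers with common correlation ρ, optimally combined, AUC = Φ(√{k d²/[1 + (k−1)ρ]}/√2). With d = 0.3 and k = 3:
- ρ = 0: √0.27 = 0.520; Φ(0.367) = 0.64.
- ρ = 0.5: √(0.27/2) = 0.367; Φ(0.260) = 0.60.

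Several markers therefore give more than the single-marker 0.58, by an amount that depends on their correlation. CTC counts are not normal, so the model is only a guide to scale.

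**The case against.** **The blind can still be achieved.** A reader might infer that it cannot hold at the bench. The documents do not support that. Frozen plasma and stored cells could be recoded and run in mixed batches after the controls arrive. This part of the objection stands.

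**Reader knowledge is not stated.** One might conclude that every PDAC-versus-control read is made with status evident. Run timing and reader knowledge are not given, so this is an inference, strongest for CTCs. Reader dependence is itself partly an assumption: the CTC phenotype is fixed in the text, and manual gating or image acceptance is not described.

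**Blinded classification is worth having.** It would be wrong to say it protects nothing. The Statistical analysis section allows a move from random forests to XGBoost and neural networks if performance disappoints, and the cut-off is chosen by the Youden index. Masking validation labels guards against retuning either on validation outcomes.

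**This is detail for a laboratory manual.** Coding lists and masked reading are often left there, and their absence from an article is not an error. The Highlights sentence has the liquid biopsy as its subject, so it may be meant to cover the assays. But codes alone cannot hide an order that the article itself fixes, and that part of the concern survives.

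**Conclusion.** The concern holds in a limited form. The case-first, control-last supply from a separate source makes PDAC-versus-control status inferable for any assay read on receipt, whatever the label. The blind as worded secures the classification step only. Bias in reader-dependent marker values would enter in discovery and recur in validation undetected.

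Whether such bias occurs, and how much, cannot be settled from the article. The illustrative AUCs rest on assumed shifts, normal equal-variance markers and, for several markers, equal shifts and an assumed correlation; they are not estimates for this study. The change is worth making because it protects the central validation claim at modest cost.

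**What to change.** - State who is masked, at which step and in which phase.
- Where storage allows, run stored plasma and cells under neutral codes that hide source and date, in mixed case-control batches in random order, after the controls of that phase have arrived.
- For assays acquired on receipt, fix acquisition settings in advance and archive images and raw files under neutral codes. After the last control of each phase, score patient, benign and control files in one masked, randomly ordered session with locked gates. Use only those reads in the model.

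The supply order, and with it the age and sex matching, can stay as planned. No new samples or readers are needed.

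The costs are a coding list, the re-reading of stored files (up to 355 participants across both phases) and final marker values only at the end of each phase. Choices made at acquisition cannot be masked afterwards, and readers who made provisional reads may remember some files, so the residual risk should be acknowledged.
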